### Sample size and statistical analysis

To date, no large studies have evaluated the use of a smartphone app to improve adherence to NOACs using pill count measurements. Thus, precise sample size calculation is not possible. We assumed that drug adherence would be 91% in the control group and 95% in the intervention group with a standard deviation of 17%, considering previous studies (30, 34, 35). With a two-tailed alpha of 0.05, power of 0.95, and a dropout rate of 10%, 1,042 patients (521 patients in the intervention and 521 patients in the control groups) are required.

Categorical variables will be reported as frequencies (percentages), and continuous variables will be expressed as means ± standard deviations or medians with interquartile ranges. Categorical variables will be compared using Pearson's chi-square test or Fisher's exact test, and continuous variables will be compared using Student's *t*-test or the Mann–Whitney *U* test.

Intention-to-treat analyses will include all randomized patients. Efficacy endpoints will be mainly analyzed using the full analysis set, which includes all randomly assigned participants who underwent at least one assessment of the primary endpoint. We will also perform a per-protocol sensitivity analysis, including all patients who completed the study protocol. In the subgroup analyses, we will evaluate the differential effects of the intervention on the primary outcomes with respect to sex, age and other comorbidities.

All tests will be two-tailed, and a *P*-value <0.05 will be considered statistically significant. Statistical analyses will be performed using R version 4.2.0 (The R Foundation for Statistical Computing, Vienna, Austria).

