## Methods and analysis

### Study design

The ReInforcement of adherence Via self-monitoring app Orchestrating biosignals and medication of RivaroXaban in patients with Atrial Fibrillation and co-morbidities (RIVOX-AF) study is a prospective, randomized, open-label, nationwide, multicenter trial to evaluate the efficacy of smartphone apps (MEDI-app) in improving drug adherence to NOACs in patients with AF. Thirteen tertiary university hospitals in South Korea will participate in this study. Enrollment began in March 2022, is currently ongoing, and is expected to be completed in late 2023. The study design has been registered at ClinicalTrials.gov (NCT05557123).

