** *Inclusion criteria:* **
1. Patients with AF aged 19 years or older with one or more comorbidities including heart failure, myocardial infarction, stable angina, hypertension or diabetes mellitus (Patients can be enrolled 3 months after myocardial infarction or percutaneous coronary intervention). 2. Patients with AF who are taking or initiating newly-prescribed rivaroxaban 3. Patients who can use a smartphone and are fluent in Korean 4. Patients who voluntarily consent to participate in this clinical trial

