### Patient recruitment and randomization

Any patient who comes to the clinic for AF management will be considered a potential participant. After a comprehensive interview, eligible participants will be asked to provide written consent for participation in the trial. A baseline survey covering demographics and cardiovascular comorbidities will be given to eligible participants (Table 2). These data will be collected by a research nurse, who will re-interview the patient and refer to the doctor's notes. Then, using a web-based central randomization service (http://matrixmdr.com), eligible participants will then be randomly assigned to either the intervention group (MEDI-app) or the conventional treatment group in a 1:1 ratio. It will not be possible to blind the participants to group allocation owing to the nature of the intervention.

**Table 2 T2:** Standard protocol items: Recommendation for interventional trials (SPIRIT) check list.

	STUDY PERIOD			
	Enrolment	Allocation	Post-allocation	Close-out
TIMEPOINT	Day -28 to 0	Visit 1 (day 0)	Visit 2 (12 weeks)	Visit 3 (24 weeks)
ENROLMENT:				
Eligibility screen	X			
Informed consent	X			
Allocation		X		
INTERVENTIONS:				
Intervention (MEDI-app)		♦——————————————————————————♦		
Control (Conventional Treatment)		♦——————————————————————————♦		
ASSESSMENTS:				
Baseline characteristics	X			
Drug adherence		X	X	X
Secondary endpoints			X	X

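### The article names only unadjusted two-sample tests; adjusting for hospital, user status and, once defined, day-0 adherence would gain modest precision on the primary endpoint

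*Protocol article*

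**What the plan says.** Under Sample size and statistical analysis, the article states: "Categorical variables will be compared using Pearson's chi-square test or Fisher's exact test, and continuous variables will be compared using". For continuous variables the choice is a t-test or a Mann–Whitney test. The sentence follows the descriptive summaries and covers all variables of each type. No covariate, regression model or stratification factor is named. Patient recruitment and randomization says only that patients are "randomly assigned to either the intervention group (MEDI-app) or the conventional treatment group in a 1:1 ratio".

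Other parts of the article bear on this:

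- **Day-0 measurement.** The Table 2 row "Drug adherence" is marked at Visit 1 (day 0) as well as at Visits 2 and 3. No analysis uses the day-0 entry.
- **Mixed population.** Table 1 admits "Patients with AF who are taking or initiating newly-prescribed rivaroxaban". Study population also lets in patients on other NOACs once they have switched.
- **Sites.** "Thirteen tertiary university hospitals in South Korea will participate in this study".
- **Endpoint.** Study outcomes defines adherence as pills dispensed minus pills returned, divided by the days from dispensing to follow-up, assessed at 12 and 24 weeks.
- **Sample size.** "We assumed that drug adherence would be 91% in the control group and 95% in the intervention group with a standard deviation of 17" per cent, leading to "1,042 patients (521 patients in the intervention and 521 patients in the control groups) are required".

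**The concern.** The primary endpoint is a continuous ratio, and the sample size compares two means. The only stated methods that fit it are the t-test and the Mann–Whitney test, neither of which uses anything known about the patient at entry.

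Three such items are available or nearly so. Hospital is known for everyone. User status (established, switched or new) has to be established when eligibility is checked. Adherence at day 0 is on the visit schedule. If any of these predicts later adherence, the assumed SD of 17 points contains variance that a model could remove.

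Precision is what is at stake. The article itself says that a precise sample size calculation was not possible and, under Limitations and strengths, that its calculation may be inaccurate. If the true difference is below 4 points, recoverable variance matters more than it does at the planned effect.

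**Working it through.** **Inputs from the article:** difference 95 − 91 = 4 points; SD 17; two-sided alpha 0.05; power 0.95; dropout 10%; 521 per arm.

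**1. Reproduce the plan's figure.** The number per arm is 2 × SD² × (1.960 + 1.645)² / difference² = 2 × 289 × 12.995 / 16 = 469.4. Dividing by 0.9 gives 521.6. The stated 521 per arm (1,042 in total) agrees; rounding up at each step would give 470, then 523 per arm, or 1,046. With 521 × 0.9 ≈ 469 evaluable per arm, the standard error is 17 × √(2/469) = 1.110. Power is Φ(4/1.110 − 1.960) = 95.0%.

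**2. Effect of adjustment.** A covariate with correlation r to the outcome reduces the residual variance to 17² × (1 − r²). If only a fraction f of patients has a value, this becomes 17² × (1 − f·r²). The documents give neither r nor f, so both are assumptions. All rows use 469 per arm.

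| Assumption | Variance removed | SE | Power, 4 points | Power, 3 points |
|---|---|---|---|---|
| Unadjusted | 0% | 1.110 | 95.0% | 77.1% |
| r = 0.3, all have a value | 9% | 1.059 | 96.5% | 80.9% |
| r = 0.5, all have a value | 25% | 0.961 | 98.6% | 87.7% |
| r = 0.3, half have a value | 4.5% | 1.085 | 95.8% | 79.0% |
| r = 0.5, half have a value | 12.5% | 1.038 | 97.1% | 82.4% |

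Example from the last row: 3/1.038 = 2.89, and Φ(2.89 − 1.96) = 82.4%.

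**3. Hospital alone.** If 1% to 10% of the variance lies between hospitals (assumption), power at 4 points is 95.2% to 96.7%.

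**4. Cost of the extra terms.** The full model adds 12 terms for hospital, 2 for user status and 1 for day-0 adherence, so 15. With 938 evaluable patients, covariates that predicted nothing would inflate the variance of the arm difference by about 15/920 = 1.6%. The SE would be 1.119 and power at 4 points 94.7%. The figures in steps 2 and 3 do not include this small loss. It roughly cancels the gain from hospital if hospital explains only 1%.

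**5. Is there a day-0 value to use?** The formula needs an earlier dispensing date and returned tablets. If dispensing is at day 0, the denominator is zero days. New starters have no earlier supply, and switchers have no earlier rivaroxaban supply. For established users the tablets were dispensed before the trial, and the article does not say how they are to be counted. As written, the day-0 entry is scheduled but undefined.

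**The case against.** The other side has several good points.

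- **The tests are valid.** Under 1:1 randomisation the unadjusted difference is unbiased, and the sample size was built on the unadjusted SD. This stands in full. A reader might infer that the planned test or the sample size is wrong; the documents do not support that.
- **The sentence is generic.** It is not tied to the primary endpoint, and a full protocol or SAP may specify an adjusted model. That is possible. But it is the only stated method that fits a continuous outcome, and an adjusted primary analysis would depart from it.
- **Chance imbalance is not bias.** A reader might infer that an uneven split of new and established users would pass uncorrected into the result. The standard error already allows for this. Suppose half are new users and they differ by 10 adherence points (both assumed). The typical imbalance is √(0.25 × 2/469) = 3.3 percentage points, which shifts the difference by about 0.33 points against an SE of 1.11.
- **Day-0 adherence is not a free covariate for everyone.** This stands: new starters and switchers have no prior rivaroxaban count. The Table 2 mark could also mean only that counting starts then.
- **The predictors are not shown to be strong.** The article gives no evidence on how far earlier adherence, user status or hospital predicts the outcome. User status is not among the baseline items it lists.

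What remains is that a better-specified comparison is available at small cost.

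**Conclusion.** The point holds as a recommended improvement in precision. It does not show an error in the test or the sample size. At the planned 4-point difference the gain is small, because power is already 95.0%: up to 96.5–98.6% if every patient has a usable day-0 value, and 95.8–97.1% if half do. It is more useful if the true difference is 3 points: from 77% to 81–88% with all values, or to 79–82% with half.

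These ranges rest on assumed correlations of 0.3 to 0.5 and an assumed share of patients with a day-0 value. Because new starters and switchers are eligible, the half-available rows are the safer guide, although their actual share is not given. The one defect that needs no assumption is that Table 2 schedules a day-0 adherence measure which the formula under Study outcomes cannot produce when dispensing is at day 0.

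**What to change.** Before the data are analysed:

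1. **Define the day-0 measure.** State what is counted, from which dispensing date and for which patients. Take it before allocation is disclosed, since the trial is open-label. If the Table 2 mark means only the start of counting, say so and leave this covariate out.
2. **Name the primary model.** For adherence at 12 and at 24 weeks, fit a linear model with arm, hospital and user status at entry (established, switched or new).
3. **Add day-0 adherence for established users only.** Set it to a constant for new starters and switchers. The user-status factor then acts as the missing indicator; a separate indicator would be collinear with it.
4. **Report** the adjusted mean difference with its 95% CI, and keep the unadjusted test as supportive.

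The cost is wording in the analysis plan, recording user status for every patient (the research nurse already interviews patients and consults the doctor's notes), modest extra analysis work and 15 model terms among about 938 evaluable patients. The sample size need not change.

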### Study outcomes

The primary endpoint of the study is adherence to rivaroxaban at 12 and 24 weeks. Drug adherence will be evaluated with the “pill count” measurements. The patients brought the remaining tablets to each scheduled visit, and trained and certified research nurses counted the number of returned drugs and calculated drug adherence as follows:$$\begin{array}{rl} & \mathrm{Drug}\;\mathrm{adherence}\;=\\ & \frac{\mathrm{number}\;\mathrm{of}\;\;\mathrm{pills}\;\mathrm{dispensed}-\mathrm{number}\;\mathrm{of}\;\mathrm{pills}\;\mathrm{returned}}{\mathrm{number}\;\mathrm{of}\;\mathrm{days}\;\mathrm{between}\;\mathrm{dispensing}\;\mathrm{date}\;\mathrm{and}\;\mathrm{follow}-\mathrm{up}\;\mathrm{date}} \end{array}$$In addition, we will evaluate the concordance of drug adherence by pill count measurements and app-calculated indices.

The key secondary endpoints are clinical composite endpoints, including systemic embolic events, stroke, major bleeding requiring transfusion or hospitalization, or death during the 24 weeks of follow-up. Other secondary endpoints include (1) major adverse cardiac and cerebrovascular events and hospitalization, (2) thromboembolism (stroke, transient ischemic attack, pulmonary embolism), (3) major bleeding requiring hospitalization or transfusion, or (4) minor bleeding. To evaluate the feasibility of the smartphone app, additional analysis will be conducted regarding the frequency of smartphone app use.

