## Discussion

This randomized controlled trial will investigate the feasibility and efficacy of smartphone apps and mobile health platforms in improving adherence to NOACs. Additionally, current study will also evaluate the benefits of app-based interventions in the reduction adverse clinical events related to AF. We believe that this prospective, randomized, large, multicenter trial will be helpful in developing public health strategies to improve NOAC adherence through smartphone use.

Poor drug adherence to NOACs may increase the risk of stroke, which may result in rising overall health care costs (14–17). Therefore, consistent drug adherence is important to maintain the effect of anticoagulation during NOAC therapy. Recently, Thakkar et al. demonstrated that mobile phone text messaging improves medication adherence in chronic disease (36). Also, Desteghe et al. showed that telemonitoring with or without feedback resulted in higher NOAC adherence (18). However, text messaging, telemonitoring, and feedback by health care providers require time, financial expenditure, and personnel and, thus, are challenging to incorporate in a real clinical setting. Today, smartphones are available to most of the general population at affordable costs. With the advent of mobile technology and advances in AI, mobile-based feedback algorithms may be promising strategies to assist in the self-management and improvement of drug adherence in chronic diseases, including AF, using cost-effective and accessible methods. We believe that our approach of using a smartphone app would be an efficient way to improve drug adherence at a minimum cost.

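### The key secondary composite, which counts deaths over 24 weeks, falls on the natural reading mainly to an analysis set that a patient who dies before any pill count cannot enter

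*Protocol article*

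**What the plan says.** The section on sample size and statistical analysis names three populations.

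- Intention-to-treat: "Intention-to-treat analyses will include all randomized patients". No endpoint is attached to it.
- Full analysis set: the "full analysis set, which includes all randomly assigned participants who underwent at least one assessment of the primary endpoint". Efficacy endpoints, in the plural, are analysed mainly in this set.
- Per-protocol: "We will also perform a per-protocol sensitivity analysis, including all patients who completed the study protocol".

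Under Study outcomes, "The primary endpoint of the study is adherence to rivaroxaban at 12 and 24 weeks", measured by pill count: "The patients brought the remaining tablets to each scheduled visit". The section on the intervention and follow-up places the first visit after randomisation at week 12. The key secondary composite covers systemic embolic events, "stroke, major bleeding requiring transfusion or hospitalization, or death during the 24 weeks of follow-up". The Discussion presents clinical events as a question of benefit: the study "will also evaluate the benefits of app-based interventions in the reduction adverse clinical events related to AF".

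**The concern.** A set that requires a week-12 or week-24 pill count suits an adherence endpoint, which does not exist without a count. It does not suit an endpoint that includes death. A patient who dies in week 6 has a composite event, and that same event keeps the patient out of the set in which the composite is mainly analysed. A patient who withdraws early and never brings tablets back is also left out, whatever happened clinically.

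Membership then depends on what happens after randomisation. The trial is open-label and only one arm uses the app, so the reasons for not returning could differ by arm. The comparison in that set is no longer strictly between the groups as randomised. With few events expected, each omitted one carries weight. The article also leaves two candidate sets for the composite with no rule for choosing between them.

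**Working it through.** **1. The plan's own figure.** The article gives no number for the analysis-set question, but its sample size supplies the denominator. Inputs from the sample-size paragraph: means of 91% and 95%, SD 17%, two-sided alpha 0.05, power 0.95, dropout 10%.

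- n per arm = 2 × [17 × (1.960 + 1.645) / 4]² = 469.4
- With dropout: 469.4 / 0.90 = 521.6 per arm, against 521 stated (1,042 in total). Rounding up to 470 first gives 523.

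The stated size reproduces, so 521 per arm is the number randomised.

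**2. Who can enter the full analysis set.** The entry rule and the visit schedule together give:

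| Patient | Pill count? | In the set? |
|---|---|---|
| Dies before week 12 | none possible | no |
| Never returns with tablets | none | no |
| Early non-fatal stroke or bleed, attends week 12 or 24 with tablets | yes | yes |
| Misses week 12, attends week 24 with tablets | yes | yes |

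Table 2 also marks drug adherence at Visit 1 (day 0). That mark cannot be a pill count under the article's formula: the denominator is the days from dispensing to follow-up, and at allocation there is no such interval and no study tablet has been returned.

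**3. Deaths excluded.** The article gives no mortality figure. Assume 1% to 3% a year, a constant hazard, and that every patient alive at week 12 has a count.

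- Deaths per arm in 24 weeks: 521 × (1 − 0.99^(24/52)) = 2.4, up to 521 × (1 − 0.97^(24/52)) = 7.3
- Deaths per arm before week 12: 521 × (1 − 0.99^(12/52)) = 1.2, up to 521 × (1 − 0.97^(12/52)) = 3.6

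About half of the deaths are lost, because 12 of the 24 weeks precede the first count.

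**4. Patients missing from the denominator.** The planned dropout is 10% of 1,042, or 104 patients. The article does not say how much of it comes before any count. Assumed shares:

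| Share of dropout before any count | Missing from the set | Remaining |
|---|---|---|
| 25% | 26 | 1,016 |
| 50% | 52 | 990 |
| 100% | 104 | 938 |

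Steps 3 and 4 may overlap, since a death may be counted as dropout. They should not be added.

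**The case against.** The strongest reply is that the article never assigns the composite to the full analysis set. It calls the composite key secondary, not an efficacy endpoint. It mixes embolic events with bleeding and death, which are often handled as safety outcomes. Mapping endpoints to sets is ordinary content for a full protocol or SAP, and neither is shown. The article also plans intention-to-treat analyses of everyone randomised and states that the trial is not powered for clinical events.

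Part of this stands. The assignment is an inference, though the natural one: the rule covers efficacy endpoints in the plural, the Discussion treats event reduction as a benefit, and no separate safety set is defined. If the composite is not an efficacy endpoint, the text gives it no set at all, and the correction is the same. The intention-to-treat sentence does not settle the matter, because it names no endpoint and the next sentence makes the pill-count set the main one. The rule is stated, so this is more than a detail left for later. Lack of power limits what can be concluded about events but is no reason to omit deaths.

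Four stronger readings are tempting and are not supported:

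- That the composite is analysed only in patients with a pill count. The text says mainly.
- That early strokes and bleeds are lost as a rule. Nothing says such an event ends participation, and one later count at either visit keeps the patient in.
- That the composite is biased in a known direction. Dropping early deaths lowers the count, but dropping event-free early losses raises the proportion, and nothing shows which arm would gain.
- That chi-square or Fisher tests are wrong here. The article gives generic tests for categorical variables, and a time-to-event method would be a preference.

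**Conclusion.** The point holds as a defect in the stated analysis-set rule. On the natural reading, the main analysis of the key secondary composite excludes patients who die before any pill count and patients who never return with tablets. That amounts to roughly 1.2 to 3.6 deaths per arm, which rests on an assumed annual mortality of 1-3%, a constant hazard and full week-12 attendance among survivors. Under the planned dropout, up to about 104 of 1,042 patients could be missing if all of it came before any count.

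The effect is on the completeness of event counts and on the validity of the randomised comparison for clinical endpoints. The sample size is unaffected, and using the full analysis set for adherence is not in question here. Some readers might go further and infer that the trial's clinical findings will be biased in favour of the app. The document gives no basis for that.

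**What to change.** State in the analysis-set paragraph that the key secondary composite and all other clinical and bleeding endpoints are analysed primarily in all 1,042 randomised patients, by assigned arm, from randomisation to 24 weeks, whether or not a pill count exists. Keep the full analysis set for the adherence endpoint. Make the change before outcome data are analysed, so that the choice between the two sets is not open afterwards.

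The wording costs almost nothing and the number randomised does not change. There is a small practical cost: Table 2 schedules secondary endpoints only at weeks 12 and 24, and the article does not describe how events are found in patients who miss visits. Their event and vital status would have to come from available records. Where it cannot be established, the plan should say whether they are treated as missing or censored.
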